## Abstract

**Background:**

Clinical prediction rules (CPRs) represent a method of determining individual patient risk to help providers make more accurate decisions at the point of care. Well-validated CPRs are underutilized but may decrease antibiotic overuse for acute respiratory infections. The integrated clinical prediction rules (iCPR) study builds on a previous single clinic study to integrate two CPRs into the electronic health record and assess their impact on practice. This article discusses study design and implementation of a multicenter cluster randomized control trial of the iCPR clinical decision support system, including the tool adaptation, usability testing, staff training, and implementation study to disseminate iCPR at multiple clinical sites across two health care systems.

**Methods:**

The iCPR tool is based on two well-validated CPRs, one for strep pharyngitis and one for pneumonia. The iCPR tool uses the reason for visit to trigger a risk calculator. Provider completion of the risk calculator provides a risk score, which is linked to an order set. Order sets guide evidence-based care and include progress note documentation, tests, prescription medications, and patient instructions. The iCPR tool was refined based on interviews with providers, medical assistants, and clinic managers, and two rounds of usability testing. “Near live” usability testing with simulated patients was used to ensure that iCPR fit into providers’ clinical workflows. Thirty-three Family Medicine and General Internal Medicine primary care clinics were recruited at two institutions. Clinics were randomized to academic detailing about strep pharyngitis and pneumonia diagnosis and treatment (control) or academic detailing plus use of the iCPR tool (intervention). The primary outcome is the difference in antibiotic prescribing rates between the intervention and control groups with secondary outcomes of difference in rapid strep and chest x-ray ordering. Use of the components of the iCPR will also be assessed.

**Discussion:**

The iCPR study uses a strong user-centered design and builds on the previous initial study, to assess whether CPRs integrated in the electronic health record can change provider behavior and improve evidence-based care in a broad range of primary care clinics.

**Trial registration:**

Clinicaltrials.gov (NCT02534987)

## Background

Patients receive only 55% of recommended care [1] along with a lot of unnecessary care [2]. While the amount of clinical evidence continues to explode, how to best integrate this evidence at the point of care remains elusive. In order to provide patients with the right care while avoiding unnecessary care, it is critical that we determine the best methods for making clinical evidence available to providers where clinical decisions are made.

Clinical prediction rules (CPRs) represent a method of determining individual patient risk to help decide what care is appropriate to give [3]. CPRs use data that can include patient history, physical exam findings, and basic lab test results to determine a patient’s risk for having a disease state. There are a number of well-validated CPRs that have been shown to be accurate and useful in reducing unnecessary care [4]. However, these CPRs are not being routinely used at the point of care and there are very few examples of integration into electronic health records (EHRs).

Overuse of antibiotics in respiratory tract infections has continued to be a major problem causing patient harm and contributing to antibiotic resistance [5–8]. We previously developed and validated an EHR-integrated clinical prediction rule (iCPR) clinical decision support (CDS) tool. The study demonstrated the tool’s ability to reduce inappropriate antibiotic prescribing and test ordering for patients with respiratory tract infections. However, it was developed and tested in a single academic health center internal medicine clinic, limiting its generalizability to more diverse settings [9]. To extend these promising findings, a new study was launched examining how these iCPR CDS tools translate to more diverse primary care settings. This article discusses the tool adaptation, usability testing, training, and implementation procedures used to adapt and disseminate the iCPR tool at diverse primary care clinics across two health care systems.

## Methods/design

The iCPR cluster randomized controlled study was designed to test the feasibility and effectiveness of incorporating strep pharyngitis and pneumonia CPRs into EHRs in diverse primary care practices. The main objective was to determine the impact of the iCPR on provider antibiotic prescribing and test ordering. This study was approved by each site’s Institutional Human Subjects Protection Review Board.

### Setting/clinic eligibility

The study is being conducted at primary care clinics associated with the University of Wisconsin and University of Utah medical centers. All General Internal Medicine (GIM) and Family Medicine (FM) primary care clinics at the two institutions were invited to participate. A total of 33 individual clinics (12 GIM clinics, 16 FM clinics, and 5 combined clinics) are participating in the study. Table 1 illustrates the clinic characteristics. Clinics were enrolled by site leads at each medical center. All physicians, nurse practitioners, physician assistants, and residents at participating clinics were eligible to participate. Both sites use the same EHR system (Epic Systems, Verona, WI) and had off-the-shelf capabilities to develop CDS tools in their EHR. Each site was supported by an information technology department that was able to develop and test the components of the iCPR before deployment.

**Table 1 Tab1:** Description of study clinics

	University of Wisconsin	University of Utah
Total no. of clinics	22	11
No. of intervention clinics	12	6
Total no. of providers	268	111
GIM clinics	10	2
FM clinics	12	4
Combined GIM and FM clinics	0	5
No. of providers per clinic	2–29	3–23

*GIM* General Internal Medicine, *FM* Family Medicine

### Randomization

A computer-generated, blocked, stratified-randomization scheme was performed at the level of the clinic. Stratification was by institution and by the number of patient visits to the clinic in the previous year that would have triggered the iCPR tool. Three strata of visits were used: <750, 750–1500, and >1500. Group assignment was performed by the study statistician.

### Intervention and control groups

Both groups received a 45-min academic detailing session that included a review of the CPRs used in the study, discussion of evidence-based diagnosis of strep pharyngitis and pneumonia, and guidelines for treating strep pharyngitis and pneumonia. Participants were given handouts with the CPRs and treatment guidelines and links to online resources. Academic detailing sessions at intervention clinics also included an overview of the iCPR tool with a live demonstration in the EHR. Participants received handouts about iCPR and links to additional online training materials. Providers that were unable to attend the academic detailing were given access to printed and online training materials. The iCPR tools were made active in the EHR for providers at intervention clinics on the day of the academic detailing, thus giving providers immediate access. Control groups did not receive access to the iCPR tools.

### Patient inclusion and exclusion criteria

Patients are included in analyses if they have a visit with a provider at a study clinic during the study period that meets iCPR triggering criteria based on reason for visit, diagnosis, or diagnosis and antibiotic ordering (Table 2). In addition, patients must meet the age criteria for tool use: ages 3 to 70 years for possible strep and ages 18 to 70 for possible pneumonia. Age cutoffs were based on the validation evidence for the CPRs [10–12]. While validation studies did not necessarily have an upper age cutoff, few patients older than 70 were included in these studies and presentation of respiratory infection may change with age. A waiver of informed consent was obtained from the Institutional Human Subjects Protection Review Board at each medical center.

**Table 2 Tab2:** iCPR triggers (reason for visit, diagnosis, and combined diagnosis/antibiotic)

Strep	Pneumonia	Both
Reason for visit		
Sore throat	Cough and/or chest congestion	
	URI symptoms	
Diagnosis		
Pharyngitis (ICD-10: J02.9, R07.0)	Cough (ICD-10: RO5)	
Strep (ICD-10: J02.0, J03.00, J03.01)	URI (ICD-10: J22, J98.8, J06.9)	
	Bronchitis (ICD-10: J20.8, J20.9, J40)	
	Pneumonia (ICD-10: J13, J18.1, J15.0, J14, J15.4, J15.3, J15.20, J15.211, J15.212, J15.29, J15.5, J15.6, J15.8, J15.9, A48.1, J18.9)	
Reason for visit and antibiotic combination^a^		
Hoarseness	Fever	
Diagnosis and antibiotic combination^a^		
Laryngitis (ICD-10: J04.0, J04.2, J05.0, J06.0)	Wheezing (ICD-10: R06.2)	Dyspnea/SOB (ICD-10: R06.89, R06.09, R06.00, R06.02)
		Fever (ICD-10: R50.9)
		Rhinitis (ICD-10: J00)

*URI* upper respiratory infection, *ICD* International Classification of Diseases, *SOB* shortness of breath

^a^Antibiotics: Oral penicillins, macrolides, cephalosporins, quinolones, tetracyclines

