### Tool design considerations

The team also reviewed all of the iCPR tool features and designs to ensure it met the needs of the diverse clinics. This included examining the (1) tool activation level, (2) timing of alerts, (3) integration into clinical workflow, (4) alert triggers, and (5) interruptive versus non-interruptive alerts.Tool activation: We chose to activate the tool based on the clinic where the encounter was performed instead of at the provider level. The clinic was chosen to coincide with the unit of randomization and to prevent study contamination from providers that worked at multiple clinics.Timing of alerts: It was clear from interviews with providers that there was variation in when they ordered tests and antibiotics during the patient encounter. We chose to base the main trigger on the reason for visit despite infrequent completion of this field by providers in the original iCPR clinical site [9]. Relying on reason for visit as the main trigger made iCPR available early in the encounter and throughout the subsequent workflow. We also included a secondary trigger, similar to the original iCPR design, that would occur toward the end of the encounter based on diagnosis and a combination of diagnosis and orders. While the secondary trigger may not be frequently used, it might allow providers to change decisions or at least alert them to considerations for future encounters. We also automatically triggered alerts in the provider’s inbox and when the provider reopened an encounter after a relevent test had resulted.Integration into clinical workflow: The iCPR needed to be integrated into active clinical practice without disrupting patient care. It is clear that without integration into workflow, CDS tools are not used [15]. This led to some individualization between institutions including the use of NoteWriter at some sites. We also decided to make iCPR as flexible as possible in order to facilitate the integration into various workflows. This included the ability for providers and nurses to use bundled ordersets based on test results and for support of telephone encounters or patient portal encounters.Alert triggers: Another guiding principle was limiting the number of inappropriate triggers. We balanced trigger sensitivity and specificity, erring on the side of specificity at the cost of missing some potentially appropriate encounters. Triggers were determined by reviewing clinic data from the previous year for the final encounter diagnoses based on available reasons for visit and whether antibiotics were prescribed. We found that only three reasons for visit commonly resulted in diagnoses that we wanted to affect. Based on these, we chose “cough/chest congestion,” “URI (upper respiratory infection),” and “sore throat” as the reason for visit triggers. For triggers based on diagnosis and antibiotics, we chose the narrowest diagnoses and only antibiotics commonly used in respiratory infections (Table 2).Interruptive vs non-interruptive alerts: Interruptive alerts interfere with workflow and force users to acknowledge the alert, potentially increasing clinician frustration and alert fatigue [16, 17]. Given the broad nature of the three reasons for visit triggers we chose, we knew that iCPR was likely to trigger at times when it would not be helpful, such as when a patient with asthma or sinusitis presented with a cough. Based on the risk of inappropriate triggers as well as provider opinions from the interviews, we chose to use non-interruptive alerts for the reason for visit triggers. We explored options for non-interruptive alerts for the diagnosis triggers, but there were no mechanisms within the EHR that allowed us to do this. Thus, we opted for interruptive alerts if iCPR was triggered by a diagnosis or diagnosis plus antibiotic prescription.

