#### Smart sets

The content of the smart sets needed to vary by the level of patient risk (low, intermediate, or high). To provide this functionality, we chose to leverage EPIC functionality which allowed suppressing components of the smart set based on patient factors (weight and age) as well as risk score. We developed one smart set for sore throat and one for cough. The smart sets included documentation for progress notes, laboratory orders, prescription orders, diagnoses, patient instructions, and level of service (Fig. 3).

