#### Clinical data collection

All clinical data will be collected via the EHR. Provider data will include level of training (physician, resident physician, NP, PA), gender, and date of birth. Provider data is stored in the provider profile within the EHR. Patient data will be collected for patients that have iCPR eligible encounters during the study period. Patient data will include date of birth, allergies, comorbidities, and any other encounters within 1 week of the qualifying encounter. Encounter data will include clinic site, date of visit, medication orders (including antibiotics), test orders (rapid strep test, throat culture, and chest x-ray), test results, diagnoses, trigger for iCPR (reason for visit or diagnosis), use of iCPR components, and score on iCPR calculator. Collection of data in the control group will use a “shadow” simulation to determine which encounters meet criteria for iCPR trigger even though the tool does not actually trigger. The final data set will be shared with the principal investigator, co-investigators, and the data-coordinating site at Boston University. The funding agency NIAID will also have access to use the data set.

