#### Clinical practice outcomes

The study outcomes were designed to evaluate changes in clinical practice related to iCPR tool use. The primary outcome is the difference in antibiotic prescribing rates in iCPR patient encounters in intervention versus control providers. Secondary outcomes include the rates of rapid strep, throat culture, and chest x-ray ordering and the class of antibiotics prescribed. To measure the safety of clinical care, we will evaluate rates of additional encounters to primary care or urgent care, hospitalization, and prescription of respiratory tract antibiotics within 1 week of the index encounter.

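### Some encounters enter the primary denominator only because an antibiotic was ordered, so for them eligibility is the outcome

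*Protocol article*

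**What the plan says.** All references are to the protocol article.

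- **Randomization:** a "stratified-randomization scheme was performed at the level of the clinic". Encounters accrue afterwards.
- **Patient inclusion and exclusion criteria:** an encounter is analysed if it "meets iCPR triggering criteria based on reason for visit, diagnosis, or diagnosis and antibiotic ordering". In Table 2, the block headed "Diagnosis and antibiotic combination" lists laryngitis, wheezing, dyspnea, fever and rhinitis. A further block pairs hoarseness or fever as reason for visit with an antibiotic. The sentence on inclusion does not mention that second pairing.
- **Clinical practice outcomes:** "The primary outcome is the difference in antibiotic prescribing rates in iCPR patient encounters in intervention versus control providers".
- **Clinical data collection:** control encounters are found by a shadow "simulation to determine which encounters meet criteria for iCPR trigger even though the tool does not actually trigger". The trigger (reason for visit or diagnosis) is among the data recorded.
- **Tool design considerations:** reason for visit is the main trigger. For the late triggers, "we opted for interruptive alerts if iCPR was triggered by a diagnosis or diagnosis plus antibiotic prescription". The secondary trigger is expected to be infrequent, but "it might allow providers to change decisions or at least alert them to considerations for future encounters".
- **Statistical analysis:** a three-level logistic model with fixed effects for intervention and randomization strata. It does not narrow the population for the primary outcome.

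**The concern.** A prescribing rate needs a denominator that is settled without reference to prescribing. Here a rhinitis visit with no other trigger is counted if an antibiotic was ordered and is absent if none was. In control clinics such visits therefore contribute prescribing of 100% by construction.

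In intervention clinics the tool acts on the same order. An interruptive alert may lead the provider to withdraw it, and a provider who has learned from earlier alerts may never place it. In the second case the visit disappears from the intervention denominator while its control counterpart stays.

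The shadow simulation makes the rule the same in both arms. It does not make the selected encounters the same, because the rule depends on behaviour that the intervention is meant to alter. The random effects and strata terms deal with clustering and design, and cannot undo selection on the outcome. At stake is the size and meaning of the primary estimate.

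**Working it through.** The article gives no figure for the share of antibiotic-conditional encounters, so there is no plan figure to reproduce. Its only related inputs, under Power calculation, are a control rate of 30–40% and an absolute decrease of 10 points. The rest is illustration on stated assumptions.

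**Inputs**
- q = prescribing rate in encounters that qualify unconditionally: 0.30 or 0.35 (assumed, within the article's 30–40%).
- f = visits with an antibiotic-conditional complaint and no other trigger, per unconditional encounter: 0.1 to 0.3 (assumed).
- g = prescribing rate in those visits, whether or not they are counted: 0.2 to 0.4 (assumed).
- e = relative reduction from the tool in all visits: 0.25 (assumed; 10 points off 40% is 10/40 = 0.25).

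**Formulas**
- Conditional share of control encounters: fg/(1 + fg), from 0.02/1.02 = 2.0% to 0.12/1.12 = 10.7%.
- Control rate: C = (q + fg)/(1 + fg).
- Intervention rate, eligibility read from final orders: (1 − e)(q + fg)/(1 + (1 − e)fg).
- Intervention rate, eligibility fixed at trigger time: (1 − e)(q + fg)/(1 + fg). This assumes that each avoided order was first placed and then withdrawn.
- Benchmark, the difference over all these visits, counted or not: e(q + fg)/(1 + f).

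**Step 1: no tool effect.** With e = 0, both intervention formulas reduce to C. The difference is exactly 0 for every f, g and q.

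**Step 2: a 25% relative effect.**

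| | f = 0.1, g = 0.4, q = 0.30 | f = 0.3, g = 0.2, q = 0.35 |
|---|---|---|
| Control rate | 0.34/1.04 = 32.69% | 0.41/1.06 = 38.68% |
| Intervention, final orders | 0.255/1.03 = 24.76% | 0.3075/1.045 = 29.43% |
| Intervention, trigger time | 0.255/1.04 = 24.52% | 0.3075/1.06 = 29.01% |
| Benchmark difference | 0.25 × 0.34/1.1 = 7.73 | 0.25 × 0.41/1.3 = 7.88 |
| Excess, final orders | 0.21 points | 1.37 points |
| Excess, trigger time | 0.45 points | 1.79 points |

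These two columns are the extremes over the whole grid: 0.21–1.37 points for final orders and 0.45–1.79 for trigger time (differences taken before rounding).

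**Step 3: is the direction fixed?** Now suppose that conditional encounters are 5% of the control arm, that the tool removes half of those orders, and that it does nothing elsewhere.
- Final orders: with a control rate of 30%, the intervention rate is (0.30 − 0.05 + 0.025)/(0.95 + 0.025) = 28.21%, a difference of 1.79 points. With 40%, it is 0.375/0.975 = 38.46%, a difference of 1.54.
- Trigger time: 0.05 × 0.5 = 2.50 points.
- Over all such visits, with 30% prescribing in the conditional complaints: 0.025/(0.95 + 0.05/0.30) = 2.24 points.

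Here the final-order reading understates the effect by 0.45–0.70 points and the trigger-time reading overstates it by 0.26. The direction is not fixed.

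**The case against.** The strongest defence is that little is affected. Reason for visit is the main trigger, the late triggers are expected to be rare, and one rule is applied to both arms. That limits the size and must be said. It is an expectation without a figure, though, and if these encounters are few, removing them costs almost nothing.

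Four stronger readings are tempting, and the document does not support them.

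- **A changed denominator could show an effect where treatment did not change.** A reader might infer this for the antibiotic-conditional triggers. Step 1 rules it out: with ordering unchanged, the same visits are selected in both arms.
- **The order sets supply diagnoses in intervention clinics only, so the tool pulls extra low-prescribing visits into that arm.** It is true that "The smart sets included documentation for progress notes, laboratory orders, prescription orders, diagnoses, patient instructions, and level of service". But under iCPR components the order set is offered only after a trigger has fired and the calculator is complete, so that encounter is already counted. Order-set support for telephone and portal contacts does not help the argument either, since inclusion requires a visit. What remains is that exposed providers might label visits differently. That is possible, but its direction and size are unknown, and both arms received detailing on diagnosis.
- **The control rate is inflated relative to the planning value.** The 30–40% under Power calculation is stated for iCPR-eligible encounters, the same population, so there is no planning mismatch.
- **Fever, wheeze or rhinitis visits count only with an antibiotic.** This is too absolute. Any that also carry cough, URI symptoms or sore throat as reason for visit, or a listed diagnosis, enter without one.

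**Conclusion.** The point holds in a limited form. Part of the primary denominator is defined by the primary outcome, and nothing elsewhere in the article removes that part from the primary analysis. For it, comparability is not protected by randomisation. This does not make the arms as a whole non-comparable: encounters entering by an unconditional reason for visit are untouched by the problem.

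The consequence is a distorted effect size when the tool works, not a spurious effect when it does not. Under the assumed 2–11% share and 25% relative effect, the overstatement is about 0.2–1.4 points (final orders) or 0.4–1.8 points (trigger time), against a planned 10. Other plausible inputs give understatement. The true share is unknown, so the actual size cannot be derived from the document.

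Selection through diagnosis-only triggers, which are also recorded after randomisation, is a secondary concern that cannot be quantified.

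**What to change.** 1. For the primary antibiotic-prescribing analysis, exclude from both arms every encounter that qualifies only through an antibiotic-conditional trigger, using one identical query. Encounters that also meet an unconditional trigger stay in.
2. Add an analysis restricted to unconditional reason-for-visit triggers (sore throat, cough/chest congestion, URI symptoms) to address possible changes in diagnostic labelling.
3. Report the number of encounters by trigger type and arm.
4. Reconcile the inclusion sentence with Table 2, which also lists reason for visit combined with an antibiotic.

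The cost is a change of wording and a filter on EHR data already being collected. There will be slightly fewer encounters, and the primary estimate will no longer cover complaints that qualify only with an antibiotic. The present denominator cannot give a proper prescribing rate for those complaints in any case.
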